### Justification for Study Design

The study is conducted nationwide and multicentrally with specially selected sites to achieve higher representativeness of the study results for the entire population. Since the study’s primary objective is to observe the effects of filgotinib therapy on QoL and psychomotor markers, a single-arm study design is warranted. Furthermore, the study aims to investigate to what extent it is possible to have an additional observational outcome tool for monitoring disease activity in patients with IBD by using wearables.

### Wearables

Since exercise and sleep are associated with QoL, 2 wearables are used in this study to enable measurement of the patients’ movement and sleep comprehensively. We hypothesize that early changes in wearable parameters (eg, increase of step counts and normalization of heart rate variability) are potentially associated with long-term improvement of QoL. Other studies show similar results. van Langenberg et al [19] reported significantly poorer sleep quality and less physical activity in patients with Crohn disease compared with healthy control subjects, as measured by an accelerometer over 7 days. Similarly, Wiestler et al [6] found significant associations between physical activity and the disease-specific QoL and disease activity in patients with IBD.

In the FilgoColitis study, 2 wearables are used. The leg accelerometry sensor SENS motion is a medical device, whereas the GARMIN smartwatch vívosmart 4 is a simple fitness watch. We aim to show that nonmedical devices can also be used in clinical studies to measure physical activity and can be related to other important outcomes. The advantages of nonmedical devices are higher affordability and easier usability. Thus, we hope to be able to scientifically demonstrate in the FilgoColitis study that less expensive, widely used devices are also suitable for the monitoring of patients with UC. Nevertheless, it must be noted that nonmedical devices can also be less valid and accurate. In an unpublished field study prior to commencement of the FilgoColitis study, we successfully showed the comparability of both wearables in an on-site test (data not shown).

To achieve meaningful results from the additional examination, the researchers are dependent on a high level of compliance from the study participants. For the success of the study, patients who voluntarily participate in the additional examination must wear their wearables at the desired times for the desired duration. However, since the FilgoColitis study is noninterventional and due to its voluntary nature in the additional examination, decreasing compliance of study participants must be expected. Because of the longer study duration, patients may forget to put the wearables back on for the visit or to transfer their data. Willingness to wear a watch or leg sensor visibly on the body may also drop over the study course. These assumptions were made based on findings from researchers in other digital studies where a decline in compliance over the course of the study was observed. One review showed that compliance is usually very high at the start of the study and then declines rapidly over the first weeks and months. However, success factors such as user training, health education, and maintaining strong participant motivation were also identified to positively influence compliance [20].

The compliance of the study participants cannot be enforced, but the framework conditions can be designed in the best possible way to achieve the highest possible compliance. Therefore, measures were also introduced in the FilgoColitis study, such as the creation of detailed instructions and web-based tutorials or active technical support by the study team. If the study size is smaller than expected due to low compliance, statistical recalculations must be performed to ensure that the results are still statistically meaningful. Nevertheless, if compliance within additional examination is so low that no meaningful results can be obtained, as a consequence the results can only be examined in relation to the primary and secondary outcome measures. However, due to the measures mentioned above, we hope to achieve the highest possible compliance of the study participants.

The use of new technologies such as smartwatches or leg sensors has many advantages in studies. Examples are higher recruitment rates, faster feasibility of the study, and the collection of a broader range of health data [21,22]. Atreja et al [23] summarize in the review on remote monitoring of patients with IBD that in the near future this rapidly evolving technology will become a mainstream tool in standard patient care practices. Nevertheless, certain obstacles must also be expected. Technical problems may occur at any time, which means that important participant movement data cannot be recorded or transmitted and is therefore lost. In addition, the additional examination is not feasible for everyone. Patients without their own smartphones cannot participate, and certain prior knowledge of smartphone use is also assumed. Due to the partly complicated procedure, older people may be excluded due to excessive demands or lack of knowledge. However, studies show that older people are generally positive about smartwatch technologies for measuring PROs. According to Manini et al [24], the aspect of user-friendliness is one of the most important points that must be given special consideration during design. Therefore, elements such as detailed explanations and descriptions, big visible buttons, and a frequently asked question area were added to the MyTARGET study app. The goal was to create the greatest possible user-friendliness, so that older study participants are also attracted to the additional examination within the FilgoColitis study.

### Strengths and Limitations

The FilgoColitis study is the first large real-world study of filgotinib. One strength is the prospective design of the study. In addition, the primary outcome parameter is a PRO, namely QoL. In particular, the assessment of fatigue represents a modern approach in IBD research. Finally, the use of new technologies that objectively measure exercise, sleep, and stress behavior makes the study unique.

The study also has some limitations: a selection bias cannot be excluded in the FilgoColitis study and should also be considered in future analyses. To recruit a broad representative population of study participants and overcome the selection bias, we distributed the study sites all over Germany and included patients with a large age range (18-80 years). In addition, physicians consecutively enrolled eligible patients in the study. Moreover, filgotinib is the first oral preferential JAK1 inhibitor, and its approval has also opened up new strategies for the treatment of patients with UC. Due to the newly emerging treatment opportunities, it can be assumed that mainly last liners, meaning patients who have already taken several biologics without success, will receive the new drug and will be included in the study. Accordingly, it can be assumed that these patients tended to be in poor health prior to study inclusion and have a low QoL. However, the effect that filgotinib may have on QoL can still be well examined by surveying QoL at baseline. Thus, individual improvement or worsening of QoL over the course of the study can be evaluated for all participants without bias regarding the prevailing health status. The selection bias is tried to be avoided accordingly.

In addition, the FilgoColitis study is conducted using written questionnaires completed by the patients and physicians. On the one hand, we do not see limitations with regard to the physicians, since the remote monitoring system allows queries to be asked at any time regarding open or unclear answers. On the other hand, however, there could be omitted questions or illogical answers with regard to the patients, which could negatively influence the analysis of the study objective. To counteract this limitation, however, the attending physicians and the trained study nurses work closely with the patient so that questions can be asked at any time in the event of ambiguities or problems. In this way, as many missings as possible are to be avoided.

Nevertheless, with our efforts to eliminate the mentioned limitations, we aim to use the observational FilgoColitis study to draw significant correlations between the QoL and psychosocial well-being of patients with UC on filgotinib therapy over the long-term course under real-world conditions. With the results of the study, we intent to assist physicians in making future treatment decisions regarding the prescription of filgotinib.

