#### Justification of Sample Size

The difference in sIBDQ scores from baseline to week 10 (week 52 and week 104) will be analyzed. The null hypothesis is that the average difference is zero. The alternative hypothesis is that the average difference has a nonzero value. Based on the results of a previous study [15], we aim to demonstrate a difference of 7 points or more with an α of .05, assuming an SD of 12, and assuming that each pair of measurements on the same individual correlates with approximately 0.5. With a sample size of 250 subjects, a power of >90% is achieved to detect the above mean of paired differences with a 2-tailed paired *t* test [16].

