### Conclusions

In summary, in the FilgoColitis study, we aim to find out how the new JAK1 inhibitor filgotinib affects the QoL of patients with UC in clinical practice with real-world conditions and how safe the therapy is. By using wearables, we assume to obtain superior data to assess patients’ QoL. We also hope to prove that the use of wearables could be an additional observational outcome tool to monitor disease activity in patients with IBD. With the multicenter approach, large study population, and long study duration, we aim to obtain meaningful and valid data on the safety and effects of filgotinib therapy.

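### Measuring QoL at baseline does not free the single-arm change score from bias due to health status at entry; regression to the mean and natural course stay mixed with any filgotinib effect

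*Protocol article*

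**What the plan says.** In Strengths and Limitations the protocol article expects mainly patients who have already failed several biologics, and says "it can be assumed that these patients tended to be in poor health prior to study inclusion and have a low QoL". It then argues that surveying QoL at baseline still allows the effect of filgotinib to be examined well, and that individual improvement or worsening "can be evaluated for all participants without bias regarding the prevailing health status". The next sentence presents this as the way in which the plan tries to avoid selection bias.

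Other sections also read the change as a drug effect. Justification for Study Design reasons that since the "primary objective is to observe the effects of filgotinib therapy on QoL and psychomotor markers, a single-arm study design is warranted". The Conclusions of the Discussion aim to find out "how the new JAK1 inhibitor filgotinib affects the QoL of patients with UC in clinical practice". The last paragraph of Strengths and Limitations intends the results to help physicians decide on prescribing.

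The Overview under Statistics calls the study descriptive and noncomparative, and defines the primary end point as the mean sIBDQ change from baseline to week 10 with its 95% CI. Justification of Sample Size nevertheless sets a null hypothesis of zero mean change and states "we aim to demonstrate a difference of 7 points or more with an α of .05".

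**The concern.** A patient's own baseline removes stable differences in level between patients. It does not remove the consequence of choosing the moment of entry. If patients tend to start therapy when they are worse than they would be at a random time, scores rise on average afterwards even if the drug does nothing. A low starting point that has been measured is still a selected starting point, and the change score is where that selection shows.

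The conditions for this are in the article. UC is described as chronic and recurrent (Background). Entry coincides with the start of in-label therapy at the physician's discretion (Participant Criteria), for a drug approved in moderate to severe active disease (Abstract). QoL at entry is expected to be low. There is no comparator. Regression to the mean and natural fluctuation are not mentioned.

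At stake is what the trial may conclude. A significant mean improvement at week 10 would be reported as what filgotinib does to QoL and offered as guidance for prescribing, with the article's assurance that health status at entry does not bias it.

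**Working it through.** **Inputs from Justification of Sample Size.** Target difference 7 points; "assuming an SD of 12"; "assuming that each pair of measurements on the same individual correlates with approximately 0.5"; N=250; two-sided α of 0.05, paired *t* test; stated power above 90%. The article does not say whether 12 is the SD of scores or of differences. At correlation 0.5 this makes no difference: SD of differences = 12 × √(2 × (1 − 0.5)) = 12.

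**Step 1, the plan's own figure.** Standard error = 12/√250 = 0.759, and 7/0.759 = 9.2. By the noncentral *t* distribution the power exceeds 99.99%, and 33 patients would already give 90%. The power statement is true.

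**Step 2, precision.** 95% CI half-width = 1.97 × 0.759 = 1.49, about 1.5 points.

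**Step 3, what the mean change contains.** Observed mean change = drug effect + natural course + regression to the mean. One arm supplies only the sum. Schedule of Visits has a single QoL assessment before treatment (week 0), so the data contain no untreated change from which to estimate the last two terms.

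**Step 4, illustrative size.** Let D be the distance of the enrolled baseline mean below the mean of the reference population from which patients are selected. With equal SDs and a stable population mean, expected change without a drug effect = (1 − ρ) × D. D is assumed, since the documents give no reference or baseline sIBDQ mean and no QoL entry threshold.

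| Assumed D (points) | ρ = 0.3 | ρ = 0.5 (planning value) | ρ = 0.7 |
|---|---|---|---|
| 5 | 3.5 | 2.5 | 1.5 |
| 10 | 7.0 | 5.0 | 3.0 |
| 14 | 9.8 | 7.0 | 4.2 |

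D = 14 is 14/12 = 1.17 SD. For normal scores it corresponds to enrolling about the lowest 30% directly on sIBDQ.

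**Step 5, indirect selection.** Patients are not selected on sIBDQ. If they are selected on an activity measure that correlates r with sIBDQ at baseline and rρ at follow-up, the same strictness of selection gives r times the regression. With r = 0.7 (assumed) and ρ = 0.5, selecting the lowest 50%, 30% and 20% gives about 3.3, 4.9 and 5.9 points, against 4.8, 7.0 and 8.4 under direct selection.

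**Step 6, consequence for the test.** A mean change of 2.5 points with no drug effect (D = 5 at ρ = 0.5) would be significant against zero with probability about 0.91. At 3.5 points (D = 7) the probability is above 0.99. Rejecting zero change is therefore no evidence of a drug effect in this design.

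**The case against.** The strongest defence is that the sentence has been read too absolutely. The same discussion of limitations opens by conceding that selection bias cannot be excluded and should be considered in later analyses. The following sentence says only that the plan tries to avoid it. The claim is limited to health status and concerns each patient measured against his or her own baseline. The statistics section calls the study descriptive. A single arm is normal for a noninterventional study, and no end point, analysis or sample size is shown to be wrong.

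Part of this stands: the point concerns interpretation and wording, not conduct, and the mean change with its CI remains a valid description. The defence does not rescue the sentence. The general caveat is answered, a few lines later, by an argument that does not work. The sentence before the quoted one applies that argument to the filgotinib effect, and the descriptive label sits beside effect wording in three sections.

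The objections to the size carry more weight:

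- The 0.5 is a planning correlation between visits on either side of the start of treatment. It is not the stability of sIBDQ without treatment.
- The formula in Step 4 applies to distance from a reference population mean, not from each patient's own usual level. A purely temporary dip below one's own level would return in full under independent errors; a lasting impairment would not return at all.
- Results reports that 90% of the first 69 patients were pretreated with biologics and that disease duration was 7.4 years. This suggests that at least part of the low QoL is lasting.

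**Conclusion.** The statement that change since baseline is unbiased with respect to health status is wrong as written, and so is the inference that the filgotinib effect can therefore be examined well. The expected direction of the distortion is towards improvement, provided that at least part of the low QoL at entry is temporary.

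The size is unknown. The 2.5, 5 and 7 points are illustrations that rest on an assumed shortfall of 5, 10 or 14 points, equal SDs at both visits, and a correlation of 0.5 borrowed from the sample size section. They fall if the impairment is lasting, if selection is indirect or if the correlation is higher, and rise if the correlation is lower.

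A reader might infer that regression to the mean accounts for the whole 7-point target, or that it outweighs any drug effect. The documents do not support this: 7 points arises only because a 14-point shortfall was put in. The narrow CI shows that the estimate will be precise, not that the bias is large. It does mean that the CI gives no protection against a bias of a few points. Nor does the point show any fault in the power statement or in the choice of the primary end point.

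**What to change.** 1. In Strengths and Limitations, delete the sentence that declares change free of bias from health status, and the following one on avoiding selection bias. Reword the preceding sentence, which says the filgotinib effect can be examined well.
2. In the same place, name regression to the mean and natural fluctuation of UC as limitations of the uncontrolled change score.
3. In Justification for Study Design, Strengths and Limitations, and Conclusions, describe the primary result as the change observed after starting filgotinib, not as its effect. Carry that wording into the results report.
4. Optionally, show a sensitivity range such as the table above beside the primary mean, with each assumption labelled. Do not subtract it from the result. Without a repeated pre-treatment QoL assessment, neither the untreated correlation nor the shortfall can be estimated from the study, and a correlation taken from on-treatment visits would not supply it.

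The cost is a few sentences and at most one table. Data collection, sample size and primary analysis stay as they are. The downside is a more modest conclusion, with less weight for prescribing decisions.

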### Conclusions

In summary, in the FilgoColitis study, we aim to find out how the new JAK1 inhibitor filgotinib affects the QoL of patients with UC in clinical practice with real-world conditions and how safe the therapy is. By using wearables, we assume to obtain superior data to assess patients’ QoL. We also hope to prove that the use of wearables could be an additional observational outcome tool to monitor disease activity in patients with IBD. With the multicenter approach, large study population, and long study duration, we aim to obtain meaningful and valid data on the safety and effects of filgotinib therapy.

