**Objective:**

The study investigates quality of life (QoL) and psychosocial well-being of patients with active ulcerative colitis during long-term exposure to filgotinib. PROs related to QoL and psychometric profiles (fatigue and depression) are collected alongside with disease activity symptom scores. We aim to evaluate physical activity patterns collected by wearables as an addition to traditional PROs, patient-reported health status, and QoL in different phases of disease activity.

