**Conclusions:**

Real-world data for novel drugs are important to assess effectiveness outside of highly selected populations represented by randomized controlled trials. We examine whether patients’ QoL and other PROs can be supplemented with physical activity patterns measured objectively. Use of wearables with newly defined outcomes represents an additional observational tool for monitoring disease activity in patients with inflammatory bowel disease.

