#### Exploratory Data Analysis

As an exploratory data analysis, correlations between the pMayo and exercise data and psychomotor data (such as sleep quality, stress, and fatigue) will be calculated.

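### The article says wearables add to PROs and give superior data on quality of life, but its stated wearable analyses are associations with no incremental comparison and cannot show added information

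*Protocol article*

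**What the plan says.** The claims about wearables are comparative. The Objective in the Abstract reads: "We aim to evaluate physical activity patterns collected by wearables as an addition to traditional PROs". The Abstract's Conclusions ask whether quality of life and other PROs "can be supplemented with physical activity patterns measured objectively". The Conclusions at the end of the Discussion go further: "By using wearables, we assume to obtain superior data to assess" patients' quality of life, followed by "We also hope to prove that the use of wearables could be an additional observational outcome tool to monitor disease activity".

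The analysis is stated under Exploratory Data Analysis in the Statistics section: "correlations between the pMayo and exercise data and psychomotor data (such as sleep quality, stress, and fatigue) will be calculated". This is the only wearable analysis given there. The mixed model for sIBDQ under Repeated Measurements Over Time names no wearable term.

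Four other places name relations of interest:
- Introduction, Objectives: association of activity patterns with health status and quality of life.
- Additional Exploratory Outcome Measures: correlation among activity, stress, sleep, disease phase and psychosocial impairment.
- The Rationale for the Study: correlation of movement measures with disease activity and fatigue.
- Discussion, Wearables: a hypothesis that early changes in wearable parameters go with long-term improvement in quality of life.

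All four are put as associations. None names a comparator, a with-and-without contrast, or a criterion for superior.

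**The concern.** To say that a measurement adds to, supplements or is superior to existing ones is to compare what is known with it and without it. A correlation with pMayo does not make that comparison. It is largest when the device reproduces pMayo, and then the device adds nothing beyond pMayo. A small correlation fits a device that measures nothing useful and equally one that carries information on quality of life that pMayo misses. Replacing pMayo by sIBDQ in the same correlation does not cure this, because a device can correlate with sIBDQ entirely through disease activity.

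The article calls the wearables the novelty of the design. If the stated analyses are carried out as written, that claim would rest on statistics that cannot separate redundant from new information on quality of life.

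**Working it through.** **The plan's own figure.** The article gives no figure for the wearable analysis. Its one power statement (above 90% with 250 patients) concerns the sIBDQ change. With SD 12 and correlation 0.5, the SD of the difference is sqrt(2 × 144 × 0.5) = 12, and power is Φ(7 × sqrt(250)/12 − 1.96) = Φ(7.26), about 1.00. The statement holds, but says nothing about wearables.

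**Inputs.**
- Number of wearers: 55 of the first 69 patients accepted (80%, Results). If that held, 0.80 × 250 = 200. This is acceptance, not sustained wear.
- Correlations: the article gives none, so all below are assumptions.

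**Formulas.** Let W be a wearable parameter, P pMayo and Q sIBDQ.
- R² with both predictors = (rPQ² + rWQ² − 2·rPQ·rWQ·rWP)/(1 − rWP²).
- Added R² = that value − rPQ² = (1 − rPQ²) × (partial r of W and Q given P)².
- 95% intervals by Fisher z with standard error 1/sqrt(197).

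**Redundant parameter.** Take rPQ = −0.7 and rWP = −0.5, with W linked to Q only through P.
- rWQ = (−0.7)(−0.5) = 0.35 (95% CI 0.22 to 0.47).
- R² = (0.49 + 0.1225 − 0.245)/0.75 = 0.49, so added R² = 0.49 − 0.49 = 0%.
- Correlation with pMayo: −0.5 (−0.60 to −0.39).

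**Informative parameter.** Take rPQ = −0.7, rWP = −0.1 and partial r = 0.3.
- rWQ = 0.07 + 0.3 × sqrt(0.51 × 0.99) = 0.283 (95% CI 0.15 to 0.41).
- Added R² = 0.51 × 0.09 = 4.6%.
- Correlation with pMayo: −0.1 (−0.24 to 0.04).

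The redundant parameter ranks higher on both correlations.

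**Sensitivity.** Sizes are shown without sign.

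| r(pMayo, sIBDQ) | r with sIBDQ, redundant | r with sIBDQ, informative | Added R², redundant | Added R², informative |
|---|---|---|---|---|
| 0.7 | 0.35 | 0.283 | 0% | 4.6% |
| 0.6 | 0.30 | 0.299 | 0% | 5.8% |
| 0.5 | 0.25 | 0.309 | 0% | 6.8% |

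The order on the sIBDQ correlation therefore depends on the assumptions. The order on the pMayo correlation (0.5 against 0.1) and the zero gain of the redundant parameter do not depend on r(pMayo, sIBDQ).

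**Simulation with other values** (4,000 runs, n = 200, size of r(pMayo, sIBDQ) 0.6).
- A redundant parameter with rWP 0.80 was significant against pMayo in 100% of runs. Its partial correlation with sIBDQ was significant in 5%, the chance level.
- An informative parameter with rWP 0.20 and partial r 0.35 was significant against pMayo in 81% of runs, and on the partial correlation in 99.9%.
- The plain correlations with sIBDQ were 0.48 and 0.39, again with the redundant parameter ahead.

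**Feasibility of an incremental analysis.** At n = 200 (two-sided 0.05), power is Φ(atanh(r) × sqrt(196) − 1.96). For a partial r of 0.20, 0.25 and 0.30 this gives 81%, 95% and 99%. With only 55 wearers, simulated power for a partial r of 0.35 was 76%.

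**The case against.** Much of the other side stands.

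- **Monitoring is also an aim.** The article wants a tool to follow disease activity. For that, agreement with pMayo is convergent validity and a proper first analysis. The watch may be worn for all 24 months, so a device that tracks pMayo between visits could be useful with no added R². The mismatch concerns only addition to PROs and superior data on quality of life.
- **Quality-of-life associations are named.** The Objectives relate activity to quality of life, and the Wearables section has a longitudinal hypothesis. Neither fixes the method as unadjusted. Neither states a comparison beyond pMayo or the PROs, however, so they narrow the gap without closing it.
- **Exploratory status.** Wearables are optional, no formal hypotheses are tested, and the wording is hedged. The article also provides for falling back on the primary and secondary outcomes if compliance is poor. This limits the weight of the point.
- **An unseen SAP may contain an incremental model.** It may. The point is not that model detail is missing, but that the article states a conclusion its stated analyses do not reach.

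A reader might infer that the plan would endorse redundant parameters and discard informative ones. The document does not support that. It contains no threshold, selection rule or decision rule; correlations are simply to be calculated. In the example above, the informative parameter has r = 0.28 with sIBDQ and an interval clear of zero, so it would be noticed under the quality-of-life aim.

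**Conclusion.** The point holds in a limited form. The stated wearable analyses can describe association and convergent validity with disease activity. They cannot show that wearables add information on quality of life, still less that the data are superior, because no comparator or incremental contrast is stated.

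The size is illustrative: plain correlations with sIBDQ of 0.35 and 0.28 can go with added R² of 0% and 4.6%. These rest on assumed correlations and 200 wearers. The two intervals overlap, and the order reverses when the pMayo–sIBDQ correlation is 0.5. What needs no assumed correlation is that the correlation with pMayo reaches its maximum exactly when the added R² is zero.

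It would go too far to say that correlating with pMayo is a wrong analysis, or that the study's main result is at risk. The primary end point is unaffected.

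**What to change.** 1. **Exploratory Data Analysis.** Keep the correlations and label them as convergent-validity description. Add an exploratory incremental analysis for sIBDQ, or for later sIBDQ change to match the hypothesis in the Wearables section. Compare a mixed model with pMayo/PRO2, age, sex and baseline sIBDQ against the same model plus a small, pre-named set of wearable parameters, both fitted to the same patients and visits.
2. **Reporting.** Give the partial association with its 95% CI, or a likelihood-ratio test, together with the out-of-sample gain (patient-level cross-validation or optimism correction). Do not use a bootstrap interval for the in-sample R² gain as the criterion. In nested least-squares models that gain cannot be negative; in a simulation with a true gain of zero and n = 200, the interval excluded zero in 100 of 100 runs.
3. **Discussion, Conclusions.** Replace the superiority wording with the question whether wearable data add information on quality of life beyond pMayo/PRO2 and baseline sIBDQ, or limit the claim to association. With sIBDQ as the outcome, the model cannot show superiority to sIBDQ itself.

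The cost is some wording and a little analysis time on data already being collected. The wearable claim may come out weaker, and the decline in wear that the article expects would reduce precision below the 200-patient figures.
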